#### Randomization, recruitment, and data collection

2.3.2

For each study unit a randomization list will be generated according to Efron procedure,^[41]^ using the IBM SPSS Statistics v.23.0. package for Windows. An appointment will be arranged with patients who meet inclusion criteria for the first interview, where they will receive the information leaflet of the study and will sign the informed consent form. Next, patients will be allocated to a study group according to the randomization list. Additionally, the patients will be asked to respond to the study questionnaires (SF-36v2 health survey questionnaire^[42]^ (Optum, Inc. license number QM048943), Revised Fibromyalgia Impact Questionnaire (FIQR),^[43,44]^ Visual Analog Scale (VAS),^[45,46]^ tender points^[47]^ and Hospital Anxiety and Depression Scale (HADS)^[48,49]^) and will take part in the activities planned for each group (see below).

Control group: Patients in the control group will receive regular clinical care in their PCC,^[50]^ which consists on an individual visit with the FM specialist, who will conduct a standardized clinical history and will inform the patient on the disease using a custom designed leaflet.

MT group: in addition to usual PC clinical care, participants will receive MT consisting of health education, exercise and cognitive-behavioural therapy, during 12 weeks in 2-hourly weekly sessions (Fig. 2). Group therapy will be delivered by the FM specialist in each PCC, with the support of the physiotherapist and the psychologist of the USCSS.

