#### Masking

2.3.3

Due to the study characteristics (pragmatic trial), it is not possible to mask the health professionals and participants. The data analyst will be blind to the patients’ allocation group.

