#### Outcomes

2.3.4

The main result variable of the study is quality of life (SF-36v2).^[42,51]^ Table 1 shows the study variables, the measurement instruments and the timing of data collection. All variables will be collected for both study groups. The cost-utility variables will be collected at 2 time points: 1 year before the beginning of the study and 1 year after the beginning of the study.

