#### Statistical analysis

2.3.5

Data analysis will take place at baseline and after 3, 9, and 15 months. Intention to treat analysis will be used. The quality of data collection will be periodically monitored to minimize biases due to incomplete data. The non-response bias will be evaluated at all points of follow up. Descriptive analyses of variables will be carried out using the media (standard deviation), median (interquartile range) or frequency (percentage), depending on the distribution of variables.

For comparisons between and within the 2 study groups (intervention and control) and the study variables, the following tests will be used: Student's *t* test for independent or paired data, McNemar, Chi-square test and analysis of variance or the corresponding non-parametric tests.

To evaluate the effectiveness of the intervention at each point of follow up, we will calculate the change in scores of the SF-36 and the other questionnaires in the intervention group minus the change in the control group, and the standardized effect size (SES). The SES will be calculated as the difference of the mean of the scores of both groups divided by the combined standard deviation. To detect differences within each study group, the difference of the means between baseline and each follow up point will be calculated, and also the effect size or standardized mean response (SMR), in accordance with Kazis’ method.^[52]^ The SMR will be calculated as the mean change divided by the standard deviation of change. To evaluate the SMR and the SES we will use Cohen rule, which classifies effect size as small (0.2 to 0.5), medium (0.5 to 0.8), and large (greater than 0.8).

Finally, multiple linear regression models will be used to explore the variables associated with the percentage change [(follow-up scores minus baseline scores)/baseline scores × 100] of the scores in the SF-36 and other questionnaires. The multivariate models will include variables that might be clinically linked, and the variables statistically significant in the previous bivariate analyses. Models will be also adjusted by confounding variables. Interactions and collinearity will be evaluated.^[53]^ Statistical significance for all study tests will be set at α ≤ 0.05 and 95% CI. The statistical package IBM SPSS Statistics v.23.0.for Windows will be used.

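### As written, the baseline questionnaires come after allocation in an open trial whose effect measure is change from baseline, and nothing readable says they are completed before the arm is disclosed

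*Protocol article*

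**What the plan says.** Section 2.3.2 (Randomization, recruitment, and data collection) describes the first interview. Patients receive the leaflet and give written consent. Introduced by the word *Next*, the text continues: "patients will be allocated to a study group according to the randomization list. Additionally, the patients will be asked to respond" to the study questionnaires. After listing the instruments, that same sentence ends with the patients' part in the arm-specific programme: "and will take part in the activities planned for each group (see below".

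Section 2.3.3 (Masking) states that "it is not possible to mask the health professionals and participants"; only the data analyst is blind. Section 2.3.4 (Outcomes) fixes the main outcome: "The main result variable of the study is quality of life (SF-36v2", a questionnaire that the patient answers.

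Section 2.3.5 (Statistical analysis) uses the baseline in two ways. Effectiveness at each follow-up is "the change in scores of the SF-36 and the other questionnaires in the intervention group minus the change in the control group", and the regression models take as outcome the "percentage change [(follow-up scores minus baseline scores)/baseline scores × 100". The same section also defines a standardized effect size from the difference between the mean scores of the two groups, and commits to intention to treat.

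**The concern.** A baseline is useful in a randomised comparison because the allocation cannot have influenced it. If patients answer once they know their arm, that protection is lost. One arm has just been offered 12 weekly group sessions and the other an individual visit with a leaflet, so relief or disappointment could colour the answers. FIQR, VAS and HADS are also the patient's own report. The tender-point count is exposed as well, because the professionals are unmasked.

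A blinded analyst cannot repair this, because the distortion is already in the recorded data. It enters the between-arm difference in change directly. It also enters the percentage change through both numerator and denominator, and it follows the baseline into any model that adjusts for it. It could create an apparent effect or hide a real one.

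**Working it through.** **The plan's own figure.** Section 2.3.1 gives two-sided alpha 0.05, beta 0.05, difference 5, common SD 10 and 20% dropout. Then n = 2 × (1.960 + 1.645)² × 10² / 5² = 104 per arm, and 104 / 0.80 = 130. The stated 130 per arm is reproduced. The order of steps at the first interview does not affect it.

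**Number analysed.** The plan's calculation needs 104 evaluable per arm. Planned recruitment is 14 units with 10 to 12 patients per group, or 140 to 168 per arm. Less 20%, this leaves 112 to 134. I use 104 and 134 as the ends of the range.

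**Assumptions not in the article.** These are the shift b in mean baseline between arms caused by knowing the allocation (1 or 2 units), and the correlation r between baseline and follow-up (0.5 or 0.7). SD 10 is taken as the SD of a score at each time point.

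**Formulas, with no true effect and a shift that has gone by follow-up** (Φ is the standard normal distribution function):
- Change score: bias of size b; SD of change = 10 × √(2(1 − r)); SE = SD × √(2/n).
- Baseline-adjusted comparison: bias of size r × b; residual SD = 10 × √(1 − r²); SE = SD × √(2/n).
- Rejection rate = Φ(−1.96 + bias/SE) + Φ(−1.96 − bias/SE).

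Worked case: n = 104, r = 0.5, b = 1. The SD of change is 10, SE = 10 × √(2/104) = 1.387, and bias/SE = 0.721. The rejection rate is Φ(−1.239) + Φ(−2.681) = 0.111.

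| n per arm | r | b | Change score: rejection | Adjusted: bias | Adjusted: rejection |
|---|---|---|---|---|---|
| 104 | 0.5 | 1 | 0.111 | 0.5 | 0.070 |
| 104 | 0.7 | 1 | 0.154 | 0.7 | 0.109 |
| 104 | 0.5 | 2 | 0.303 | 1.0 | 0.132 |
| 104 | 0.7 | 2 | 0.461 | 1.4 | 0.293 |
| 134 | 0.5 | 1 | 0.130 | 0.5 | 0.076 |
| 134 | 0.7 | 1 | 0.184 | 0.7 | 0.126 |
| 134 | 0.5 | 2 | 0.374 | 1.0 | 0.157 |
| 134 | 0.7 | 2 | 0.561 | 1.4 | 0.361 |

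Against the 5-unit target, 1 unit is 1/5 = 20% and 2 units are 2/5 = 40%.

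**If part of the reaction persists.** When a fraction p of the shift is still present at follow-up, it cancels in the change score and the bias is (1 − p) × b. With b = 1 and p = 0.5 the bias is 0.5 unit. At n = 104 the rejection rate is then 0.065 (r = 0.5) or 0.075 (r = 0.7).

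**With baseline taken before disclosure.** b = 0, and the rejection rate returns to 0.05.

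**The case against.** The strongest reply is that the article does not show what the concern fears. It says that patients are allocated, not that they are told their arm before they answer. *Additionally* adds an item and is not strictly a time word. Drawing the next entry from a list and disclosing it to the patient are separate events. Figure 1 (the flow diagram) and Table 1 (timing of data collection) are not shown and could give another order, and a journal article condenses a fuller protocol. This stands as a limit on certainty. A reader might infer that every baseline is recorded in full knowledge of the arm; that is the natural inference but not a stated fact. It does not remove the point, however: the article does give an order, it puts allocation first, it joins the questionnaires to the arm-specific activities, and nothing readable corrects it.

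Three further objections stand in part:
- The bias equals the whole shift only if the reaction has gone by follow-up. The commitment in section 2.5 to invite controls to the next therapy group also bears on how much disappointment to expect.
- Not every effect measure is exposed. The standardized effect size, as worded, need not use the baseline.
- The shifts and correlations are assumptions, so the rejection rates illustrate sensitivity and do not estimate a bias in this trial.

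It may also be tempting to exclude patients whose baseline was taken after allocation. That would drop randomised patients from the main comparison, against the intention-to-treat commitment in section 2.3.5.

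**Conclusion.** The point holds as a criticism of the text. Followed as written, section 2.3.2 takes the baseline after allocation in an unmasked trial, and section 2.3.5 then builds the difference in change and the percentage change on it. A reaction to allocation that shifts the baseline and does not persist biases the difference in change by that amount. Baseline adjustment shrinks the bias to r times the shift (half of it only when r = 0.5) and does not remove it.

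For a 1-unit shift that has fully faded, the false-positive rate of the change-score test is about 11–15% with 104 evaluable per arm, and about 13–18% with 134, for r between 0.5 and 0.7. The article gives no size or direction for a shift. It therefore does not support the conclusion that the trial's result is biased, or biased in favour of the therapy. What it supports is that the stated order leaves the main comparison open to a bias that can be avoided at almost no cost.

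**What to change.** Amend section 2.3.2 to say that the SF-36, FIQR, VAS, HADS and tender-point count are completed and saved in the study application after consent and before the next entry on the randomization list is revealed, at the same visit. Check that Figure 1 and Table 1 agree. The cost is two steps reordered within one existing visit and a sentence reworded, with no extra visit or patients and no change to the sample size. If sites already work this way, only the wording changes.

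For any patients already handled in the other order:
- keep everyone in the main analysis as randomised, and do not exclude those with a post-allocation baseline;
- report the order as a limitation;
- add a between-arm comparison of follow-up scores that does not use the baseline.

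With SD 10 and 104 per arm, that added comparison has SE 1.387 and power Φ(5/1.387 − 1.96) = Φ(1.65) ≈ 0.95 for 5 units, which is the power the plan already aims for. It escapes the baseline distortion, although any reaction to allocation that lasts to follow-up remains in it. The cost is one additional analysis.

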**Figure 2 F2:**
[figure not shown]
Content of the multicomponent therapy sessions.

Patients in the control and MT groups will receive an appointment to attend their PCC at 3, 9, and 15 months after the beginning of the study. During these appointments they will be asked to respond to the study questionnaires (SF-36, FIQR, VAS, tender points and HADS).

All data will be collected in a software application that has been custom designed for the treatment protocol of FM in the study sites. This application will be available in the *Terres de l’Ebre* ICS website and will be linked to the electronic medical records. The application aims to standardize all information related to patients with FM who visit the USCSS and will be used for research and for clinical care.

#### Masking

2.3.3

Due to the study characteristics (pragmatic trial), it is not possible to mask the health professionals and participants. The data analyst will be blind to the patients’ allocation group.

#### Outcomes

2.3.4

The main result variable of the study is quality of life (SF-36v2).^[42,51]^ Table 1 shows the study variables, the measurement instruments and the timing of data collection. All variables will be collected for both study groups. The cost-utility variables will be collected at 2 time points: 1 year before the beginning of the study and 1 year after the beginning of the study.

**Table 1 T1:**
[figure not shown]
Study variables, measurement instruments and timing of data collection.

#### Statistical analysis

2.3.5

Data analysis will take place at baseline and after 3, 9, and 15 months. Intention to treat analysis will be used. The quality of data collection will be periodically monitored to minimize biases due to incomplete data. The non-response bias will be evaluated at all points of follow up. Descriptive analyses of variables will be carried out using the media (standard deviation), median (interquartile range) or frequency (percentage), depending on the distribution of variables.

For comparisons between and within the 2 study groups (intervention and control) and the study variables, the following tests will be used: Student's *t* test for independent or paired data, McNemar, Chi-square test and analysis of variance or the corresponding non-parametric tests.

To evaluate the effectiveness of the intervention at each point of follow up, we will calculate the change in scores of the SF-36 and the other questionnaires in the intervention group minus the change in the control group, and the standardized effect size (SES). The SES will be calculated as the difference of the mean of the scores of both groups divided by the combined standard deviation. To detect differences within each study group, the difference of the means between baseline and each follow up point will be calculated, and also the effect size or standardized mean response (SMR), in accordance with Kazis’ method.^[52]^ The SMR will be calculated as the mean change divided by the standard deviation of change. To evaluate the SMR and the SES we will use Cohen rule, which classifies effect size as small (0.2 to 0.5), medium (0.5 to 0.8), and large (greater than 0.8).

Finally, multiple linear regression models will be used to explore the variables associated with the percentage change [(follow-up scores minus baseline scores)/baseline scores × 100] of the scores in the SF-36 and other questionnaires. The multivariate models will include variables that might be clinically linked, and the variables statistically significant in the previous bivariate analyses. Models will be also adjusted by confounding variables. Interactions and collinearity will be evaluated.^[53]^ Statistical significance for all study tests will be set at α ≤ 0.05 and 95% CI. The statistical package IBM SPSS Statistics v.23.0.for Windows will be used.

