#### Study design and sample size

2.3.1

We will carry out a pragmatic randomized clinical trial (type: parallel group) with patients suffering from FM to compare the effect of a multicomponent therapy with usual clinical care in PC. The intervention will be structured in study units. Each study unit consists of a MT group and a control group, each with 10 to 12 participants. Assuming an alpha error of 0.05 and a beta error of 0.05 in a bilateral contrast, and an estimated dropout rate of 20%, a sample size of 130 participants in each group of the study will be required in order to detect a score difference equal or higher than 5 units in the Short Form 36 (SF-36) health survey questionnaire. A common standard deviation of 10 is assumed. Based on these calculations, we will create a total of 14 MT groups, with their respective control groups, between April and December 2019. The number of participants estimated is 336 patients.

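### The effectiveness estimate is a visit-by-visit difference in change scores with no adjustment for baseline score or randomisation unit, which costs precision that a standard model would recover

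*Protocol article*

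**What the plan says.** Under Statistical analysis, effectiveness is evaluated separately at each follow-up: "we will calculate the change in scores of the SF-36 and the other questionnaires in the intervention group minus the change in the control group", together with a standardised effect size (SES). The tests listed for comparisons are t tests, McNemar, chi-square, analysis of variance and non-parametric equivalents. Neither baseline score nor study unit is named in any of these comparisons. The same section states "Intention to treat analysis will be used" and says that non-response bias will be evaluated at every follow-up.

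Multiple linear regression comes last in that section. Its task is to explore which variables are associated with percentage change. Covariates are chosen by clinical link, by significance in bivariate analyses, and as unnamed confounders. The abstract differs: there, the within-group standardised response and the SES are themselves assessed with multiple linear regression.

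On the design, Randomization, recruitment, and data collection says: "For each study unit a randomization list will be generated according to Efron procedure". Study design and sample size plans 14 units, each with an MT group and a control group of 10 to 12 patients.

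**The concern.** Two pieces of information that the trial will hold anyway are not used well in the effectiveness estimate.

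- **Baseline score.** Subtracting baseline fixes its slope at 1. The best linear slope is r when the SDs at baseline and follow-up are equal, so a change score over-corrects whenever r is below 1. Baseline adjustment estimates the slope and cannot do worse, apart from one degree of freedom. It also corrects for chance baseline imbalance.
- **Study unit.** Patients are randomised within units, but unit is absent from the comparison. Any difference between units in average change therefore stays in the error term.

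At stake are wider confidence intervals than the data require at 3, 9 and 15 months and, if r is low, power slightly under the level used for sizing. The mismatch between the abstract and the methods also leaves open which analysis carries the effectiveness claim.

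**Working it through.** **Inputs from Study design and sample size.** "Assuming an alpha error of 0.05 and a beta error of 0.05 in a bilateral contrast"; a difference of 5 SF-36 units; "A common standard deviation of 10 is assumed"; 20% dropout; "a sample size of 130 participants in each group of the study will be required"; 14 units; 336 patients in total.

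**Inputs assumed.** The baseline to follow-up correlation r is not given, so a range of 0.3 to 0.8 is used. The SD of 10 is read as the SD of scores, equal at baseline and follow-up and in both arms. The article does not say whether it is the SD of scores or of change.

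**Step 1: reproduce the stated size.** n per arm = 2 × (1.960 + 1.645)² × 10² / 5² = 103.96, so 104. With dropout, 104 / 0.80 = 130 per arm. The article's figure is reproduced exactly.

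**Step 2: evaluable number actually planned.** 14 units × 2 arms × 12 = 336, or 168 per arm. 168 × 0.80 = 134.4, so about 134 per arm.

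**Step 3: variances.**
- Change score: 10² × 2(1 − r)
- Baseline-adjusted: 10² × (1 − r²)
- Ratio: 2(1 − r) / [(1 − r)(1 + r)] = 2 / (1 + r)

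The ratio does not depend on the value of the SD.

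**Step 4: power for 5 points at 134 per arm.** Power = Φ(5 / (SD × √(2/134)) − 1.960), with √(2/134) = 0.1222. At r = 0.3:
- Change score: SD = 10 × √1.4 = 11.83; 5 / (11.83 × 0.1222) = 3.46; Φ(1.50) = 93.3%.
- Adjusted: SD = 10 × √0.91 = 9.54; 5 / (9.54 × 0.1222) = 4.29; Φ(2.33) = 99.0%.

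| r (assumed) | SD, change | SD, adjusted | Variance ratio | Power, change | Power, adjusted | n per arm incl. dropout for 95% power, change / adjusted |
|---|---|---|---|---|---|---|
| 0.3 | 11.83 | 9.54 | 1.54 | 93.3% | 99.0% | 183 / 119 |
| 0.4 | 10.95 | 9.17 | 1.43 | 96.2% | 99.4% | 157 / 110 |
| 0.5 | 10.00 | 8.66 | 1.33 | 98.4% | 99.7% | 130 / 98 |
| 0.8 | 6.32 | 6.00 | 1.11 | over 99.9% | over 99.9% | 53 / 48 |

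**Step 5: where the change score falls below 95%.** At 134 per arm, 95% power needs SD = 5 / (3.605 × 0.1222) = 11.35. Then 1 − r = 11.35² / 200 = 0.644, so r is about 0.36. Power falls short only below that value.

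**Step 6: interval width.** The confidence interval widens by the square root of the variance ratio: √1.54 = 1.24, √1.33 = 1.15 and √1.11 = 1.05. That is 24%, 15% and 5% wider at r = 0.3, 0.5 and 0.8.

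**Study unit.** The article gives no between-unit variance, so this loss cannot be quantified. Subtracting baseline already removes stable differences in level between units; only differences in average change remain in the error.

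**The case against.** The strongest defence is that the method is valid and the trial can afford it. A change score does use baseline, by subtraction, and under randomisation it is unbiased on average. Both arms sit inside every unit, so leaving unit out generally costs precision rather than creating bias. The planned 336 exceeds the 260 (2 × 130) that the calculation requires. If the SD of 10 is the SD of change, the change-score analysis has 98.4% power at 134 per arm and there is no shortfall. All of this stands, and it limits the point to efficiency.

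A second defence is that adjusted models are planned. This does not answer the point: the methods make those models exploratory, put them on percentage change, and name neither baseline score nor unit.

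Three stronger readings are tempting but not supported.

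- **Patients with missing visits are excluded, contrary to intention to treat.** A per-visit change score without imputation would leave them out, about 34 of 168 per arm (168 − 134) at 20% dropout. But no text excludes them, intention to treat is stated, and an article may leave the missing-data method to a fuller plan.
- **Power is 86% rather than 95%.** That figure holds for 104 evaluable per arm at r = 0.3. It belongs to the minimum size, not to the 336 planned.
- **The effect will be overstated through dropout.** Any figure for this needs outcomes among dropouts, which the article does not give.

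**Conclusion.** The point holds as a loss of precision. The stated effectiveness estimate adjusts for neither the baseline score nor the unit within which patients are randomised, and the abstract and methods disagree on what the regression models are for. The change-score variance is 11% to 54% above the baseline-adjusted variance for r from 0.8 down to 0.3. At the planned size, power stays at or above 95% unless r is below about 0.36; at r = 0.3 it is 93.3%, against 99.0% with adjustment.

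These figures rest on an assumed r, equal SDs at baseline and follow-up, and, for power, on the SD of 10 being the SD of scores. The stated 130 per group is correct on its own terms. This is not a validity failure, but it is worth changing because the remedy uses data already being collected.

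**What to change.** Make the effectiveness analysis a baseline-adjusted model. The preferred form is one linear mixed model per score over 3, 9 and 15 months, with arm-by-visit, baseline score-by-visit and study unit as terms and correlation within patient allowed for. Report the adjusted arm difference with its confidence interval at each visit, and base the SES on that difference. A separate baseline-adjusted regression at each visit, with study unit, is a simpler alternative.

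The mixed model also lets the earlier visits of later dropouts inform the 15-month contrast. It does so under missing at random, which should be stated; patients with no follow-up visit still contribute nothing to it.

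Revise the abstract and the Statistical analysis section so that they name the same effectiveness analysis, and keep the percentage-change regressions as exploratory.

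The cost is a change of wording and slightly more programming in the same software. With 14 units, the unit term takes 13 degrees of freedom (14 − 1) out of about 268 evaluable patients (2 × 134). No new data are needed.

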**Methods and analysis::**

A 2-phase, mixed methods study has been designed following Medical Research Council guidance. Phase 1: Pragmatic randomized clinical trial with patients diagnosed with FM that attend one of the 11 PCCs of the ICS *Gerència Territorial Terres de l’Ebre*. We estimate a total sample of 336 patients. The control group will receive usual clinical care, while the multicomponent therapy group (MT group) will receive usual clinical care plus group therapy (consisting of health education, exercise and cognitive-behavioural therapy) during 12 weeks in 2-hourly weekly sessions. Analysis: the standardized mean response and the standardized effect size will be assessed at 3, 9, and 15 months after the beginning of the study using multiple linear regression models. Utility measurements will be used for the economic analysis. Phase 2: Qualitative socio constructivist study to evaluate the intervention according to the results obtained and the opinions and experiences of participants (patients and professionals). We will use theoretical sampling, with 2 discussion groups of participants in the multicomponent therapy and 2 discussion groups of professionals of different PCCs. A thematic content analysis will be carried out.

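### The regression models take percentage change from baseline as outcome and choose covariates by significance in the same data; model the follow-up score adjusted for baseline, with covariates fixed in advance

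*Protocol article*

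**What the plan says.** Section 2.3.5 (Statistical analysis) has two layers. For effectiveness at each follow-up, "we will calculate the change in scores of the SF-36 and the other questionnaires in the intervention group minus the change in the control group", together with a standardized effect size. A last paragraph then brings in regression: "multiple linear regression models will be used to explore the variables associated with the percentage change". The outcome is given by formula as the "percentage change [(follow-up scores minus baseline scores)/baseline scores × 100] of the scores in the SF-36 and other questionnaires".

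Covariates are variables with a plausible clinical link "and the variables statistically significant in the previous bivariate analyses". In addition, "Models will be also adjusted by confounding variables"; these are not named, and the baseline score is not mentioned. No rule is given for a baseline of zero.

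The abstract (Methods and analysis) says that the standardized mean response and standardized effect size "will be assessed at 3, 9, and 15 months after the beginning of the study using multiple linear regression models". It does not mention percentage change.

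Section 2.3.1 sizes the trial on an absolute SF-36 difference of 5 units with SD 10, two-sided alpha 0.05, beta 0.05 and 20% dropout: 130 per group, with 336 patients planned.

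**The concern.** Putting the baseline in the denominator has four consequences.

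- A patient with baseline zero has no outcome and leaves the model.
- Equal gains and losses do not cancel.
- A small baseline inflates the ratio, so measurement error and regression to the mean at the low end drive the result.
- The scale differs from the one that justified the sample size.

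Covariate entry by significance is a separate fault. The covariate set is unknown until the data are seen, and ordinary standard errors and 95% intervals ignore the selection. This matters most for any model from which a treatment effect is quoted. In a pure predictor search the outcome problem still applies, because variables related to a low baseline will tend to appear as predictors of response.

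**Working it through.** **1. The plan's own sample size.** n per arm = 2 × (1.96 + 1.645)² × 10² / 5² = 103.96, so 104 evaluable; 104 / 0.8 = 130. This reproduces the stated figure and rests on the absolute scale.

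**2. Asymmetry.** One patient moves from 10 to 20, another from 80 to 70. Mean change is (10 − 10) / 2 = 0. Percentage changes are +100% and −12.5%, with mean (100 − 12.5) / 2 = +43.75%.

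**3. Zero baselines.** The ratio divides by baseline, so it does not exist at zero. For an SF-36 score with SD 10 and an assumed mean of 35, zero lies 3.5 SD below the mean, about 0.02% of patients under normality. The risk therefore lies mainly with scores that can reach zero, such as a tender-point count. The article does not give score ranges.

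**4. Power for an arm effect.** The setting was 104 per arm, SD 10, difference 5, two-sided 0.05, 2,000 simulated trials per cell, scores held at 5 or above. Baseline mean and correlation are assumptions, since the document gives neither. Entries are power in % at correlations 0.3 / 0.5 / 0.7.

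| Baseline mean | Percentage change | Percentage change, adjusted for baseline | Absolute change | Follow-up score adjusted for baseline |
|---|---|---|---|---|
| 50 | 78.3 / 90.2 / 98.7 | 94.3 / 97.6 / 99.7 | 86.0 / 95.2 / 99.6 | 97.0 / 98.7 / 99.8 |
| 40 | 69.6 / 85.2 / 97.4 | 87.8 / 94.1 / 99.2 | 84.6 / 94.6 / 99.6 | 96.8 / 98.1 / 100 |
| 35 | 62.9 / 79.4 / 95.1 | 81.9 / 90.8 / 98.9 | 86.1 / 94.6 / 99.6 | 96.2 / 98.6 / 100 |
| 30 | 56.6 / 73.9 / 93.3 | 75.2 / 87.4 / 97.6 | 85.8 / 94.6 / 99.7 | 96.2 / 98.4 / 99.8 |

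Unadjusted percentage change is below both absolute change and the baseline-adjusted score in every cell. A separate simulation over the same means and correlations gave about 50% to 98% for percentage change and 96% to 100% for the adjusted score. The low end depends on how many very small baselines are let through. The loss against the adjusted score runs from about 1 point (99.8 − 98.7 at mean 50, correlation 0.7) to over 40 points (96 − 50 at the low end).

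At the planned recruitment, 336 / 2 = 168 per arm and 168 × 0.8 = 134 evaluable. For mean 35 and correlation 0.5 the powers there are 87% (percentage change), 98% (absolute change) and 99.6% (adjusted score).

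**5. Influence of low baselines.** In the same SD 10 scenarios, the tenth of patients with the lowest baselines carries 29% to 62% of the variance of percentage change.

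**6. A score that does reach its floor (illustration only).** Assume a 0 to 100 score with mean 30, SD 20, difference 8 and correlation 0.5 or 0.7. About 7% of baselines are zero and drop out. Power is 26% to 39% on percentage change against 91% to 98% for the adjusted score, and the lowest tenth carries about 85% of the variance. These inputs are not the protocol's.

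**7. Covariate selection.** With m independent noise candidates tested at 0.05, the chance that at least one enters is 1 − 0.95^m: 40% for m = 10 and 64% for m = 20. The article does not give the number of candidates.

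**The case against.** The strongest reply is that these regressions are not the effectiveness analysis. Section 2.3.5 evaluates effectiveness by the between-group difference in absolute change and reserves regression for exploring associations; it does not even say that arm is in the models. Absolute change has about 95% power at correlation 0.5, which is the design target. This stands, and it limits the weight of the point.

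The reply also has force on size. The power loss rests on assumed means and correlations and can be as small as about 1 point. If the unnamed confounders include the baseline score, power on percentage change rises to 75% to 99.7%, although in no scenario does it exceed that of the adjusted follow-up score.

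Three stronger readings are tempting, and the document does not support them:

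- A reader might infer that losing zero-baseline patients breaks intention to treat for the trial. It would remove them from these models only; the absolute-change comparison keeps them.
- A reader might infer that the patients lost are the most severely affected. That fails for scales on which zero means no symptoms, such as a tender-point count, and zero is improbable for an SF-36 score with SD 10.
- A reader might infer from the abstract that percentage change is the effectiveness endpoint. The abstract never mentions it, and section 2.3.5 computes both effect sizes from means and standard deviations.

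What the reply does not answer is that both choices are written into the plan, and that the abstract assigns regression a role for which only this model is defined.

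**Conclusion.** The point holds at moderate severity. Percentage change is a poor regression outcome by construction: undefined at zero, asymmetric and dominated by low baselines. These properties follow from the formula. For an arm effect it is also less powerful than the baseline-adjusted follow-up score in every scenario examined: about 50% to 98% against 96% to 100%. The direction was constant, while the size depends on baseline means and correlations that the document does not give. Selection by bivariate significance undermines the reported precision of any treatment effect taken from such a model.

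None of this invalidates the main effectiveness result, which section 2.3.5 bases on absolute change. The mismatch between the abstract and section 2.3.5 over what regression is for needs to be reconciled.

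**What to change.** 1. In all regression models, replace percentage change with the follow-up score, and include arm and baseline score.
2. For any model that reports a treatment effect, fix the covariates before the data are seen and delete entry by bivariate significance.
3. Keep predictor searches if wanted, labelled exploratory. Report percentage change descriptively only.
4. Make the abstract and section 2.3.5 agree on which analysis assesses effectiveness.

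The absolute-change comparison need not be withdrawn on account of this point.

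The cost is analysis wording. The questionnaires are already planned at entry and at 3, 9 and 15 months, so no extra data, visits or patients are needed. The only loss is percentage improvement as a modelled quantity; it can still be described.
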